### 3. STUDY METHODS

#### 3.1 Trial Design/framework

The SPAARK trial is a patient-blinded, multi-centre, active comparator, randomised, controlled, two-arm, parallel group, superiority trial (RCT) comparing the effectiveness of liposomal bupivacaine hydrochloride + bupivacaine hydrochloride versus bupivacaine hydrochloride alone on post-operative recovery (systemic and local) in patients undergoing knee replacement surgery.

Liposomal bupivacaine hydrochloride is a local anaesthetic injected to provide long acting pain relief through encapsulating the active component (bupivacaine hydrochloride) within multi-vesicular liposomes. The intervention in this study is liposomal bupivacaine hydrochloride delivered together with bupivacaine hydrochloride, with a view of targeting both immediate and long lasting pain relief. This will be compared with a control of bupivacaine hydrochloride on its own.

#### 3.2 Randomisation and Blinding

Randomisation between intervention and control will be 1:1, and will be stratified by study centre and operation type (Total Knee Replacement (TKR) or Unicompartmental Knee Replacement (UKR)). Randomisation will be performed using the RRAMP internet system provided by the Oxford Clinical Trials Research Unit (OCTRU). Where possible, randomisation will occur in theatre at the time of surgery either by a member of the clinical research team or a member of the surgical team. If not possible, randomisation can occur on days prior to the surgery to allow for time to coordinate the drug supplies and inform the operative and anaesthetic team. If consent has occurred more than a day before randomisation, the local research team will verbally check the patient still agrees to participation before proceeding with randomisation.

Full details of the randomisation are available in SPAARK\_RBP\_v3.0\_19Apr2018, stored in the confidential statistical section of the TMF.

The patient will be blinded to the treatment allocation. Unblinding will be performed on an individual basis as clinical need dictates. Surgeons who administer the medication cannot be blinded to treatment allocation; however, blinding of surgeons and outcome assessors is not necessary as the two co-primary outcomes are patient reported measures.

#### 3.3 Sample Size

The trial has been powered for two primary endpoints, QoR-40 at 72 hours and cumulative pain score from 6-72 hours, with adjustment for multiplicity using the Bonferroni method [16]. The trial will be assessed as providing evidence of a difference if either of the two primary endpoints is statistically and clinically significant.

The study requires 240 patients per treatment arm in order to be 90% powered to detect a 5 point difference in global QoR-40 score between groups at a significance level of 0.025 (2-sided, adjusted for multiplicity) assuming the standard deviation is 15.5 [17]. To allow for 4% loss to follow-up this has been inflated to 500 patients (250 per treatment arm).

The study also requires a minimum of 225 patients per treatment arm in order to be 90% powered to detect a standardised difference of 33% between groups in cumulative pain score calculated as area under the curve from 6 to 72 hours post-surgery at a significance level of 0.025 (2-sided, adjusted for multiplicity). Inflating the sample size to 500 patients (250 per treatment arm) will allow for 10% loss to follow up on this variable.

Therefore a total of 500 patients will be randomised (250 per treatment arm).

Checks of the sample size calculations are detailed in the documents PAIN\_SS\_mar2016.rtf and QoR40\_SS\_mar2016 both stored in the confidential statistical section of the TMF.

### 3.4 Statistical Interim Analysis, Data Review and Stopping guidelines

The Data and Safety Monitoring Committee (DSMC) is a group of independent experts external to the trial who will assess the progress, conduct, participant safety and, if required, critical endpoints. The DSMC follows the charter as described in the document SPAARK\_DSMC\_Charter\_v1.0\_18Jan2017 stored in the TMF. The DSMC will review accruing data and summaries of the data presented by treatment group. They will assess the screening algorithm against the eligibility criteria. They will also consider emerging evidence from other related trials or research and review related SAEs that have been reported. Full details of the interim analyses planned are available in the Interim Statistical Analysis Plan, SPAARK\_Interim Statistical Analysis Plan\_V2.0\_19Jul2018 stored in the confidential statistical section of the TMF. Formal comparative interim analyses of the co-primary outcomes are not planned during the trial. The DSMC may advise the chair of the TSC at any time if, in their view, the trial should be stopped for ethical reasons, including concerns about participant safety. DSMC meetings will be held at least annually during the recruitment phase of the study.

### 3.5 Timing of Final Analysis

The final analysis of all primary and secondary endpoints will be conducted together when all recruited patients have completed all follow-up.

### 3.6 Blinded analysis

A blinded analysis of the data (not separated by treatment group) will be undertaken prior to the final data lock in order to look into the distribution of variables, missing data distributions, outliers, and to finalise the per protocol population.

### 3.7 Statistical Analysis Outline

The primary objective of improved patient recovering will be assessed by analysing the two primary endpoints: global QoR-40 scores at 72 hours and cumulative pain score from 6 to 72 hours following surgery. The QoR-40 is a global measure of quality of recovery. It incorporates five dimensions of health: patient support, comfort, emotions, physical independence, and pain; each item is graded on a five-point Likert scale. QoR-40 scores range from 40 (extremely poor quality of recovery) to 200 (excellent quality of recovery) [18]. The null hypothesis that there is no difference between the treatment arms will be rejected if either of these outcomes are statistically different at the 2.5% significance level. The trial will be considered to have a positive result if either of the dual primary outcomes returns a positive result.

Pain scores will be assessed daily in the evening at approximately 6, 24, 48, and 72 hours post-surgery, using a 0-10 VAS and cumulative pain scores will be calculated as area under the curve.

Both of the primary outcomes will be analysed using multivariate linear regression adjusting for stratification factors and other important prognostic variables, including baseline scores in the case of the QoR-40. The adjusted mean difference between the two groups together with 97.5% confidence intervals will be reported for each of the primary outcomes. If either of the primary outcomes is not normally distributed, transformation to normality will be the first approach. If this is not possible, then non-parametric techniques without adjustment will be used.

As secondary analyses both pain and QoR-40 measured at 6, 24, 48 and 72 hours will be assessed using longitudinal methods to take account of the multiple-time points and the correlation between them. Multi-level, multivariate linear regression modelling with adjustment for the same factors as the primary analysis will be used. Other continuous variables will be analysed using similar methodology. For binary variables the number and percentage of patients in each category will be reported for each treatment group and overall. Chi-squared tests will be utilised for comparing the treatments, with additional analyses being undertaken using multi-variate logistic regression with adjustment for stratification and other important prognostic factors if sufficient events have been observed.

Reporting of the results will be based on the CONSORT statement.

It is anticipated that all statistical analysis will be undertaken using Stata (StataCorp LP, [www.stata.com](http://www.stata.com)) or other well-validated statistical packages.

## 4. STATISTICAL PRINCIPLES

### 4.1 Statistical Significance and Multiple Testing

A significance level of 0.025 will be used and 97.5% confidence intervals will be presented for each of the two primary outcomes. The trial will be considered to have a positive result if either of the dual primary outcomes returns a positive result at this significance level.

All secondary analyses will be considered as supporting the primary analysis and will be analysed using a significance level of 0.05 with 95% confidence intervals.

Interim analyses of primary and secondary endpoints will not be carried out unless requested by the DSMC. In this case, p-values of 0.001 will be used for significance.

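### Plain Bonferroni for the two primary outcomes is valid but gives up power on the second one; Holm would recover it within the same 5% family-wise bound

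*Combined protocol and SAP*

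**What the plan says.** The two primary outcomes are QoR-40 at 72 hours and the area under the pain curve from 6 to 72 hours. SAP 3.3 powers the trial for both, "with adjustment for multiplicity using the Bonferroni method", and protocol 11.2 says the same. SAP 4.1 sets the level: "A significance level of 0.025 will be used and 97.5% confidence intervals will be presented for each of the two primary outcomes". The success rule follows: "The trial will be considered to have a positive result if either of the dual primary outcomes returns a positive result at this significance level". Protocol 11.1 and 11.3 and SAP 3.7 agree.

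The power calculation uses the same level. For QoR-40, SAP 3.3 states: "The study requires 240 patients per treatment arm in order to be 90% powered to detect a 5 point difference in global QoR-40 score", "at a significance level of 0.025 (2-sided, adjusted for multiplicity) assuming the standard deviation is 15.5". For pain it asks for at least 225 per arm to detect a standardised difference of 33% with 90% power. Loss allowances of 4% and 10% bring both to 250 per arm.

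Neither document lets the second outcome be tested at a higher level once the first is significant.

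**The concern.** The either-outcome rule decides whether the trial is positive, but it does not cover everything the trial sets out to claim. The primary objective (SAP 2.2, Table 1; protocol section 5) covers systemic and local recovery. Each half has its own outcome, its own 90% power calculation, and its own adjusted difference and p-value in SAP Table 10. Readers will take each as a separate claim.

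With two hypotheses, once one is rejected at 0.025 the other can be tested at 0.05 without breaking the 5% family-wise limit. Fixed Bonferroni leaves that allowance unused. At stake is the chance of supporting the second outcome, and so both halves of the objective, when both effects are real.

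**Working it through.** **Inputs (SAP 3.3 and 3.2).** QoR-40: difference 5, SD 15.5, 240 per arm. Pain AUC: 0.33 SD, 225 per arm. Two-sided 0.025 each, 1:1 allocation. The correlation between the two test statistics, signed so that benefit on both is positive, is not given; 0 to 0.9 is assumed.

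**Reproducing the plan.** n per arm = 2 (SD/difference)² (z₀.₉₈₇₅ + z₀.₉₀)², with z values 2.2414 and 1.2816.
- QoR-40: 2 × 3.1² × 3.523² = 238.5, so 239 (240 by noncentral t). Plan: 240.
- Pain: 2 × 3.523² / 0.33² = 227.9, so 228; with one third SD, 223.4, so 224. Plan: 225.
- Loss: 240/0.96 = 250 and 225/0.90 = 250.

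The plan's figures hold.

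**Family-wise error under Holm.**
- Both nulls true: a false rejection needs the smaller p-value below 0.025, exactly as under Bonferroni. The probability is at most 0.05. Simulated rates were the same for both methods: 0.0493, 0.0465 and 0.0360 at correlations 0, 0.5 and 0.9.
- One null true: a false rejection needs that p-value below 0.05, so the probability is again at most 0.05. At correlation 0 and about 90% power on the other outcome it is 0.025 + 0.90 × 0.025 = 0.0475, or about 0.048, against 0.025 under Bonferroni.

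Neither argument uses the dependence between outcomes.

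**Power, both planned effects true.** Expected z = standardised effect × √(n/2): 0.3226 × √120 = 3.534 for QoR-40 and 0.33 × √112.5 = 3.500 for pain.
- At 0.025: Φ(3.534 − 2.241) = 0.902 and Φ(3.500 − 2.241) = 0.896.
- At 0.05: Φ(3.534 − 1.960) = 0.942 and Φ(3.500 − 1.960) = 0.938.

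Holm's gain for one outcome is the probability that it falls between the two thresholds while the other is significant at 0.025. At correlation 0 this is a product: (0.9422 − 0.9019) × 0.896 = 0.036 for QoR-40 and (0.9382 − 0.8959) × 0.902 = 0.038 for pain. Other correlations use the bivariate normal distribution. With 240 and 225 per arm (%, Bonferroni → Holm):

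| Correlation | QoR-40 | Pain AUC | Both | At least one (either method) |
|---|---|---|---|---|
| 0 | 90.2 → 93.8 | 89.6 → 93.4 | 80.8 → 88.2 | 99.0 |
| 0.5 | 90.2 → 93.2 | 89.6 → 92.8 | 83.1 → 89.2 | 96.7 |
| 0.9 | 90.2 → 92.1 | 89.6 → 91.9 | 86.7 → 91.0 | 93.0 |

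With 250 per arm analysed, the gains for QoR-40 and pain are 3.4 and 2.9 points at correlation 0, 2.9 and 2.4 at 0.5, and 2.1 and 1.4 at 0.9.

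**Other outcome has no effect.** With 90% power for the first outcome, Holm's gain is 0.10, 0.16 and 0.06 points at correlations 0, 0.5 and 0.9.

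**The case against.** The strongest reply is that nothing is broken. Bonferroni controls the error, is stated consistently in both documents and is the level used for the sample size. Success needs only one outcome, and Holm leaves that probability untouched. All of this stands. It also rules out the stronger readings a reader might infer: that the multiplicity plan is wrong, that the trial is underpowered, or that Holm would make a positive trial more likely. Nor do the documents make success on both outcomes a criterion or power for it.

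A second reply is that Holm adds only p-values between 0.025 and 0.05. For QoR-40 the standard error is 15.5 × √(2/240) = 1.415, so these are observed differences of about 2.8 to 3.2 points (1.96 and 2.2414 times 1.415), below the 5-point target. For pain they are about 0.185 to 0.211 SD, against 0.33. SAP 3.3 and protocol 11.2 also ask for clinical significance. The arithmetic is right, but the documents set no clinical threshold, and treating the target difference as one is an assumption. It would equally discount Bonferroni rejections at QoR-40 differences between about 3.2 and 5 points.

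Third, the correlation is unknown and could be high, since pain is one of the QoR-40 dimensions (SAP 3.7). That stands; the gain shrinks as correlation rises.

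Fourth, under the current plan each 97.5% interval agrees with its test. That is a legitimate reason to prefer Bonferroni, and Holm gives it up for the second outcome.

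**Conclusion.** The point holds as a cheap improvement, not as a correction. Holm rejects everything that Bonferroni rejects and sometimes more. If both planned effects are real, each outcome gains about 3 points of power at correlation 0.5, and the chance of showing both rises by about 6 points. That rests on the plan's own effect sizes and SD, normal unadjusted tests, and an assumed correlation. If only one effect is real, there is almost nothing to gain.

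It would be too strong to say that Holm has the same family-wise error rate. The 5% bound is shared and the rates are equal when both nulls are true, but with one true null Holm uses up to about 0.048 where Bonferroni uses 0.025. Keeping plain Bonferroni would be defensible.

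**What to change.** Before data lock and any comparative analysis:
- State the two-step rule in SAP 4.1, and align 3.3 and 3.7: order the two p-values; test the smaller at 0.025; only if it is significant, test the larger at 0.05. Leave the either-outcome success rule and the sample size as they are.
- Amend protocol 11.1 to 11.3, or record and justify the departure as protocol 11.5 and the SAP introduction provide. SAP 6.2 already does this for the change in AUC method.
- Keep the 97.5% intervals in Table 10 and add a note: a second outcome with p between 0.025 and 0.05 is significant under Holm although its 97.5% interval includes zero.

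The cost is a few sentences and possibly a protocol amendment, with no extra patients or data. The lasting downside is the possible mismatch between test and interval.

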### 4.2 Definition of Analysis Populations

Populations for analysis are defined as follows:

Intention to treat (ITT): all participants randomised in their randomised groups.

Per protocol (PP): participants who received the allocated intervention will be analysed according to the treatment they actually received. Participants will be excluded from the PP population if:

- They did not receive the treatment to which they were randomised
- They did not provide sufficient follow-up data for analysis
- They did not satisfy the eligibility criteria for the study

The definition of the PP analysis population will be finalised during a blinded analysis of the data (not separated by treatment group) prior to the final data lock.

## 5. TRIAL POPULATION AND DESCRIPTIVE ANALYSES

### 5.1 Representativeness of Study Sample and Patient Throughput

The flow of participants through the trial will be summarised as outlined in Figure 1. This will include the number of individuals screened, eligible, randomised to each group, receiving allocated treatment and included in the primary analysis as suggested in the CONSORT guidelines. Reasons for ineligibility, loss to follow-up and exclusion from the primary analysis will be summarised, as will the number of patients who withdraw before each analysis time point.

**Figure 1: CONSORT flow diagram for participants in trial.**

[figure not shown]

## 5.2 Withdrawal from treatment and/or follow-up

The numbers (and percentages) of withdrawals by each time point will be reported by treatment group along with reasons for these withdrawals. These will be summarised as outlined in Table 2. Any differential losses will be investigated. Any deaths (and their causes) will be reported separately.

**Table 2:** Details of withdrawals from follow-up (and reasons) split by treatment group

| Questionnaire                            | Intervention |   | Control |   |
|------------------------------------------|--------------|---|---------|---|
|                                          | n            | % | n       | % |
| Withdrawals (before surgery)      | X            | X | X       | X |
| Reason 1                                 | X            | X | X       | X |
| Reason 2                                 | X            | X | X       | X |
| ...                                      | X            | X | X       | X |
| Withdrawals (day 0)               | X            | X | X       | X |
| Reason 1                                 | X            | X | X       | X |
| Reason 2                                 | X            | X | X       | X |
| ...                                      | X            | X | X       | X |
| Withdrawals (day 1)               | X            | X | X       | X |
| Reason 1                                 | X            | X | X       | X |
| Reason 2                                 | X            | X | X       | X |
| ...                                      | X            | X | X       | X |
| Repeat for subsequent time points |              |   |         |   |

## 5.3 Baseline Comparability of Randomised Groups

The baseline comparability of the two treatment groups (liposomal bupivacaine + bupivacaine hydrochloride versus bupivacaine hydrochloride alone) will be considered. The treatment groups will be compared in terms of stratification factors (see Table 3), baseline characteristics (see Table 4), and primary and secondary outcome measures at baseline (see Table 5). Numbers (with percentages) for binary and categorical variables and the number of available observations with means (and standard deviations), medians (with inter-quartile ranges) and range for continuous variables will be reported. These will be reported for each treatment group and overall. There will be no tests of statistical significance nor confidence intervals for differences between randomised groups on any baseline variable.

**Table 3:** Stratification factors at baseline – split by treatment group and overall

| Stratification factor  | Intervention |   | Control |   | Total |   |
|------------------------|--------------|---|---------|---|-------|---|
|                        | n            | % | n       | % | n     | % |
| Centre          |              |   |         |   |       |   |
| Site 1                 | X            | X | X       | X | X     | X |
| Site 2                 | X            | X | X       | X | X     | X |
| Site 3                 | X            | X | X       | X | X     | X |
| ...                    | X            | X | X       | X | X     | X |
| Type of surgery |              |   |         |   |       |   |
| TKR                    | X            | X | X       | X | X     | X |
| UKR                    | X            | X | X       | X | X     | X |

**Table 4:** Baseline characteristics of participants – split by treatment group and overall

|               | Intervention |           |              |       | Control |           |              |       | Total |           |              |       |
|---------------|--------------|-----------|--------------|-------|---------|-----------|--------------|-------|-------|-----------|--------------|-------|
|               | n            | Mean (SD) | Median (IQR) | Range | n       | Mean (SD) | Median (IQR) | Range | n     | Mean (SD) | Median (IQR) | range |
| Age    | X            | X (X)     | X (X,X)      | (X,X) | X       | X (X)     | X (X,X)      | (X,X) | X     | X (X)     | X (X,X)      | (X,X) |
| BMI    | X            | X (X)     | X (X,X)      | (X,X) | X       | X (X)     | X (X,X)      | (X,X) | X     | X (X)     | X (X,X)      | (X,X) |
|               | n            |           | %            |       | n       |           | %            |       | n     |           | %            |       |
| Gender |              |           |              |       |         |           |              |       |       |           |              |       |
| Male          | X            |           | X            |       | X       |           | X            |       | X     |           | X            |       |
| Female        | X            |           | X            |       | X       |           | X            |       | X     |           | X            |       |
| Knee   |              |           |              |       |         |           |              |       |       |           |              |       |
| Left          | X            |           | X            |       | X       |           | X            |       | X     |           | X            |       |
| Right         | X            |           | X            |       | X       |           | X            |       | X     |           | X            |       |

**Table 5:** Primary and secondary outcome measures at baseline – split by treatment group and overall

|                        | Intervention                      | Control                           | Total                             |
|------------------------|-----------------------------------|-----------------------------------|-----------------------------------|
|                        | N, mean (SD), median (IQR), range | N, mean (SD), median (IQR), range | N, mean (SD), median (IQR), range |
| QoR 40          | X, X (X), X (X, X), (X, X)        | X, X (X), X (X, X), (X, X)        | X, X (X), X (X, X), (X, X)        |
| Pain VAS (0-10) | X, X (X), X (X, X), (X, X)        | X, X (X), X (X, X), (X, X)        | X, X (X), X (X, X), (X, X)        |
| EQ-5D utility   | X, X (X), X (X, X), (X, X)        | X, X (X), X (X, X), (X, X)        | X, X (X), X (X, X), (X, X)        |
| EQ-5D VAS       | X, X (X), X (X, X), (X, X)        | X, X (X), X (X, X), (X, X)        | X, X (X), X (X, X), (X, X)        |
| OKS             | X, X (X), X (X, X), (X, X)        | X, X (X), X (X, X), (X, X)        | X, X (X), X (X, X), (X, X)        |
| AKSS            | X, X (X), X (X, X), (X, X)        | X, X (X), X (X, X), (X, X)        | X, X (X), X (X, X), (X, X)        |

